#### Analysis of endpoints

The study results will be reported in adherence to the extension of the CONSORT statement from 2010 on reporting of randomized trials [25]. Summary statistics will be used to describe and compare patient characteristics of all suitable, but non-included patients and all included patients (overall and stratified for the two treatment arms). Study endpoints will be analyzed for the intention-to-treat (ITT) population and the per-protocol (PP) population. Sensitivity analysis will be conducted for the ITT population. Thereby, the ITT population includes all randomized patients in the groups to which they were randomly assigned, regardless of their adherence with the entry criteria, regardless of the treatment they actually received, and regardless of subsequent withdrawal or deviation from the protocol. In the PP population, all protocol violators, including anyone who switched groups or missed measurements, are excluded. For each group, a number of participants (denominator) included in each analysis and whether the analysis was by original assigned groups will be given. Additional sensitivity analysis will be used if, despite all efforts taken to ensure complete data collection, the number of missing data is non-negligible or could potentially bias the results and conclusions.

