### Interventions

All patients will receive standard preoperative assessment including endocrine, pulmonary function and cardiovascular assessment, psychiatric assessment, gastroscopy with Helicobacter pylori testing, and abdominal ultrasound to check for liver size and gallstones. Patients in arm A will receive a RYGB with a 180-cm-long BPL and an AL of 80 cm; the group B will receive a RYGB with an 80-cm BPL and a 180-cm AL. The individual technique in terms of trocar position, materials used (i.e., staplers, trocar, suture) will be left to the choice of each individual surgeon. Total small bowel length will be measured during surgery; patients with a total small bowel length of less than 440 cm will be excluded from the study. Patient- and observer-blinded pre- and postoperative follow-up will be performed. There are no strategies for patients to improve adherence to intervention protocol since this is a surgical trial. All participating centers and surgeons are experienced bariatric surgeons with a minimal total caseload of more than 200 bariatric procedures and more than 50 surgeries per year. In order to make surgeons adhere to intervention protocol, all critical surgical steps (e.g., pouch size, total bowel length measurement, technique of Roux-limb and gastroenterostomy construction, closure of mesenteric defects, and operation time) will be documented in our database. The non-adherent cases will be excluded from per-protocol analysis. There will be no criteria for modifying the operative procedures.

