### Study visits

Physicians blinded to the intervention will perform study documentation and patient assessment. Since the trial is designed as an observer and patient blinded RCT, information about the surgical procedure will not be disclosed during the follow-up examinations to any assessors. There will be 11 study visits in total. The study design flow diagram is presented in Table 1. Potential study participants will be identified by the preoperative outpatient clinic consultations. The first visit will be preoperative after informed consent is obtained. Then patients will receive their study intervention according to the preoperative randomization. Postoperatively, study visits will be performed at discharge, 3, 6, 9, 12, and 18 months and 2, 3, 4, and 5 years. Each study visit includes data collection of weight, blood tests (e.g., hemoglobin, creatinine, urea, uric acid, calcium, C-reactive protein, albumin, liver function tests, fasting glucose, HbA1c, vitamins A, B1, B6, B12, and D, parathormone, ferritin, folate, zinc, cholesterol, lipoproteins, and triglycerides), and complications. In addition, questionnaires will be also assessed to study the quality of life (Bariatric Analysis and Reporting Outcome System [BAROS] [18] and the Gastrointestinal Quality of Life Index [GIQLI] [19]), the Arts questionnaire [20] to determine postoperative determine dumping syndrome and questionnaire for quantification of frequency and severity of potential diarrhea.

**Table 1 Tab1:** Schedule of study assessments

Study periods	Screening	Intervention	Follow-up								
Visit	1	2	3	4	5	6	7	8	9	10	11
Time (day, month, year)	− 3 months	0–5 days	3 months	6 months	9 months	1 year	1.5 years	2 years	3 years	4 years	5 years
Patient information and informed consent	x										
Demographics	x										
Medical history	x										
Inclusion/exclusion criteria	x	x									
Physical examination	x	x	x	x	x	x	x	x	x	x	x
Vital signs	x	x	x	x	x	x	x	x	x	x	x
Laboratory tests	x	x	x	x	x	x	x	x	x	x	x
Randomization		x									
Operation		x									
Complications		x	x	x	x	x	x	x	x	x	x
Primary variables	x	x	x	x	x	x	x	x	x	x	x
Secondary variables	x	x	x	x	x	x	x	x	x	x	x
Questionnaires	x			x		x		x	x	x	x
Adverse events		x	x	x	x	x	x	x	x	x	x

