### Study endpoints

#### Primary endpoint

The primary endpoints are %TWL and the number of nutritional deficiencies 1, 3, and 5 years postoperatively. For the %TWL the presurgical weight (at hospital entry time of the patient) and postsurgical weight at the corresponding visit will be measured.

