### Statistical analyses

#### Sample size

Our study was designed to evaluate whether long BPL in RYGB has advantages compared to short BPL in terms of % weight loss (superiority) without compromising the safety in terms of nutritional deficiency rate (non-inferiority) at 5 years follow-up. For our primary outcome efficacy and safety, assuming a %TWL of 27 ± 10% at 5 years follow-up for short BPL with a minimal improvement of 5% TWL for long BPL to be relevant and an expected cumulative nutritional deficiency rate of 50% at 5 years follow-up with a non-inferiority margin defined at 10%, 400 patients per group will be needed to reach a power of 80% with an alpha level at 5%. For further details on calculations, see the “Analysis of endpoints” section below.

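### The per-protocol population excludes anyone with missed measurements, without limit by visit or variable, so it is selected on attendance after randomisation

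*Protocol article*

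**What the plan says.** The Protocol article, under Analysis of endpoints, plans two populations: "Study endpoints will be analyzed for the intention-to-treat (ITT) population and the per-protocol (PP) population". ITT keeps every randomised patient in the assigned arm, and neither population is named as decisive for non-inferiority. The PP rule follows: "In the PP population, all protocol violators, including anyone who switched groups or missed measurements, are excluded".

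The Interventions section already holds a separate, treatment-based exclusion. After listing the operative steps to be recorded, it says: "The non-adherent cases will be excluded from per-protocol analysis".

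The schedule is long. Under Study visits: "There will be 11 study visits in total", and "Each study visit includes data collection of weight, blood tests", followed by the remaining items. In Table 1, visits 3 to 11 are the nine follow-up visits, from 3 months to 5 years. The blood panel lists 22 items, counting liver function tests and lipoproteins as one each.

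The primary endpoint section gives three time points: "The primary endpoints are %TWL and the number of nutritional deficiencies 1, 3, and 5 years postoperatively". The Sample size section sets the safety aim as "without compromising the safety in terms of nutritional deficiency rate (non-inferiority) at 5 years follow-up" and assumes "an expected cumulative nutritional deficiency rate of 50% at 5 years follow-up".

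**The concern.** A PP population is meant to show what happens in patients who received the treatment as assigned. Group switching and surgical non-adherence serve that purpose. A missed measurement does not: it is a gap in the data that arises after randomisation and says nothing about which operation was done. Three things follow if the clause is applied as written.

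- **Selection.** The PP set depends on five years of attendance. Attendance may be related to nutritional deficiency, so the protection of randomisation is partly lost.
- **Loss of known events.** The safety outcome is cumulative over five years. A patient with a deficiency recorded at year 1 who misses the year-4 visit has a known outcome and is still removed.
- **Unclear comparison.** If ITT and PP disagree, the cause could be the treatment received or attendance, and the reader cannot tell which.

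PP is a planned analysis of a primary endpoint, and non-inferiority is the aim that drives the sample size. A large loss from PP therefore falls on the safety question.

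**Working it through.** **1. Reproduce the plan's figure.** Inputs from the Sample size section: deficiency rate 50% (taken as equal in both arms), margin 10% (taken as percentage points), power 80%, alpha 5%, 400 per arm. Sidedness is not stated there. The two-sided 95% interval under Analysis of primary endpoint corresponds to one-sided 0.025.

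n per arm = (1.96 + 0.842)² × 2 × 0.5 × 0.5 / 0.10² ≈ 393.

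This agrees with 400. One-sided 0.05 would give 310 and does not agree. For weight loss (difference 5, SD 10), n = 2 × (1.96 + 0.842)² × 10² / 5² ≈ 63 per arm, so non-inferiority sets the size.

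**2. Reserve.** Power = Φ(0.10 / √(0.5/n) − 1.96). At n = 400: Φ(2.828 − 1.96) = 80.7%. The reserve is 400 − 393 = 7 patients per arm (1.75%). The Sample size section states no allowance for loss.

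**3. Size of the PP set.** The article gives no missed-visit rate, so m below is an assumption. With independent misses and k visits required, the share kept is (1 − m)^k. The clause allows at least two readings of k.

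| m per visit | Any of 9 follow-up visits: kept, n per arm, power | Only years 1, 3, 5: kept, n per arm, power |
|---|---|---|
| 1% | 0.914, 365, 77.1% | 0.970, 388, 79.6% |
| 2% | 0.834, 333, 73.3% | 0.941, 376, 78.3% |
| 5% | 0.630, 252, 61.2% | 0.857, 343, 74.5% |
| 10% | 0.387, 155, 42.1% | 0.729, 292, 67.5% |

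Example for 5% and nine visits: 0.95⁹ = 0.630; 400 × 0.630 = 252; Φ(0.10 / √(0.5/252) − 1.96) = Φ(0.285) = 61.2%.

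**4. Clustering.** Independence is the harsh case. At the other extreme the same patients miss every visit, and the share kept is 1 − m. That leaves 380 per arm at 5% (78.7%) and 360 at 10% (76.5%).

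**5. Superiority.** Even at 155 per arm, power for a 5-point difference in weight loss is 99.3%. The cost in power falls on non-inferiority.

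**The case against.** The strongest reply is that little depends on this sentence. ITT is analysed as well and keeps all randomised patients. Sensitivity analysis is planned for ITT, with more if missing data are non-negligible. A reader might infer that the non-inferiority claim is left to a small, self-selected group. The article does not support that: nothing ties the claim to PP, and the size of the set depends on an unstated missed-visit rate and on how the clause is read. The working gives anything from 388 to 155 per arm.

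A reader might also infer that complete attenders have fewer deficiencies, so that the rule favours passing. Nothing in the article shows this. Complete attenders also have more blood tests and so more chances of a deficiency being found. A patient with gaps cannot be firmly classed as deficiency-free, which gives the exclusion some rationale. Blinding of patients and observers makes attendance that differs by arm less likely, though not impossible.

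The fall in power is not all due to this rule either. A patient without five-year data lacks them in ITT too, and the 80% was stated for 400 per group, not promised for PP.

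Finally, which measurements count could be settled in an analysis plan. That would be a full answer if the article were silent, but it states a rule. The rule is wider than its purpose, and the general promise of sensitivity analyses does not change the PP definition. All the other replies stand as limits on the size of the concern.

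**Conclusion.** The point holds as a fault in the PP definition. As written, the clause makes missing data a protocol violation, conditions PP on attendance after randomisation with unknown direction of bias, and can discard deficiency events already observed. The comparison of ITT with PP then mixes attendance with treatment received.

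Its size cannot be fixed from the article. Under the assumed rates, non-inferiority power in PP falls from 80.7% to between 73% and 42% (2 to 10% missed, any follow-up visit, independent misses). It falls to 75% or 68% (5 or 10% missed) if only years 1, 3 and 5 count, and less if misses cluster. These figures assume a 50% rate in both arms, a 10-point margin and one-sided 0.025. The point does not undermine the ITT analysis or the superiority test. It should be corrected because the planned PP check cannot be read clearly as it stands.

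**What to change.** Replace the PP sentence with text along these lines:

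*The PP population leaves out patients who switched groups, whose operation was non-adherent as documented under Interventions, or who violated an entry criterion. A missed visit or measurement is not in itself a ground for exclusion. A patient is omitted from a given PP analysis only if the primary endpoint being analysed cannot be determined; a documented deficiency event counts whatever the later attendance. Other missing data are handled by the same method and sensitivity analyses as in ITT. Non-inferiority is concluded only if supported in both ITT and PP.*

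This keeps the surgical exclusion under Interventions and the tests named under Analysis of primary endpoint. It is a few sentences in the protocol and any analysis plan, needs no new data, and should be made before unblinding.

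There are two costs. First, PP will contain patients with incomplete follow-up, whose missing data must be handled. Keeping known events while omitting undetermined event-free patients raises the observed proportion, so the number omitted per arm should be reported and the sensitivity analyses should cover them. Second, requiring both populations means that joint power cannot exceed the lower of the two, and PP drops below 80% once more than about 7 patients per arm are left out.

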#### Analysis of primary endpoint

The primary objective consists of two separate analyses, one for safety and one for efficacy. The difference in efficacy is tested by performing a Mann-Whitney *U* test, thereby releasing the assumption of normality for the proportion of weight loss. The proportion of safety events during the first 5 years in each study arm is reported, including the two-sided 95% confidence interval.

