### Study design and site

This is a multicenter, randomized, controlled, patient- and observer-blinded, superiority trial in morbidly obese patients receiving either long BPL or short BPL RYGB. All participating centers (4 university hospitals and 11 cantonal, regional, and private hospitals) have knowledge and experience in bariatric surgery and were certified as Bariatric Reference Centers by the Swiss Society for the Study of Morbid Obesity and Metabolic Disorders (SMOB). The trial has been registered on ClinicalTrials.gov under the identifier NCT04219787. This protocol has been written in accordance with the Standard Protocol Items: Recommendations for Interventional Trials (SPIRIT) guidelines (Additional file 1). The planned visit and examination schedule is presented in Fig. 1.

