### Randomization

Eligible patients, who give written confirmed consent, will be registered in the electronic data capture and management system secuTrial®, which is programmed by the Clinical Trial Unit (CTU) of the University of Basel. The database is web-based and allows online randomization stratified by the involved centers. An allocation ratio of 1:1 with a block size of 4 will ensure a balance in sample size across both groups over time. The randomization allocation will only be known to the CTU staff. Patients will be enrolled and randomly assigned by the surgeon to receive a long BPL RYGB (arm A) versus a short BPL RYGB (arm B). Figure 2 provides a schematic view of both types of RYGBs.

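### The primary efficacy test is an unstratified, unadjusted Mann-Whitney test with no planned estimate or confidence interval to set against the 5-point relevant difference in %TWL

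*Protocol article*

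**What the plan says.** In the protocol article, Analysis of primary endpoint, the efficacy comparison is fixed in one sentence: "The difference in efficacy is tested by performing a Mann-Whitney" U test. The reason given is "thereby releasing the assumption of normality for the proportion of weight loss". The only interval planned in that section belongs to the safety endpoint: "The proportion of safety events during the first 5 years in each study arm is reported, including the two-sided 95% confidence interval". The section gives no stratification factor, covariate or effect measure for %TWL.

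Other sections supply what such an analysis could use:

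- Randomization describes "online randomization stratified by the involved centers", and Study design and site counts "4 university hospitals and 11 cantonal, regional, and private hospitals", that is 15 centres.
- BMI is an entry criterion with a range of 35 to 60 kg/m², so it is known for every patient.
- Study visits has weight recorded at each visit up to 5 years.
- Sample size expresses the efficacy hypothesis in means at 5 years: 27 with SD 10 in the short-limb arm, "with a minimal improvement of 5% TWL for long BPL to be relevant".

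Analysis of secondary endpoints repeats the primary analysis for %EBMIL.

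**The concern.** The hypothesis and the analysis are in different units. The trial is sized around a mean difference with a stated threshold of relevance, but the planned efficacy result is a rank-test p-value. Because the sample size is set by the non-inferiority question on nutritional deficiency, the trial is far larger than efficacy needs, and differences well below the threshold will be significant. A p-value cannot tell readers whether the gain is nearer 2 points or 5. The protocol expects the findings to bear on surgical guidelines, so that distinction matters.

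The test also leaves design information unused. It pools centres that the randomisation keeps apart, and it takes no account of baseline BMI. The stated reason for choosing it carries little weight at this size, since a comparison of means with 400 per arm does not require normally distributed raw data.

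**Working it through.** **Inputs from the protocol article.** SD 10, relevant difference 5 points, deficiency rate 50%, margin 10 points, power 80%, alpha 5%, 400 per arm (Sample size); 15 centres (Study design and site). **Assumed, because the document gives none:** centre intraclass correlation (ICC) 0.02 to 0.10, and R², the share of %TWL variance explained by centre and baseline BMI, 0.10 to 0.20 (wider values as a check).

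**1. The plan's sample size.** Non-inferiority at one-sided 2.5%: (1.96 + 0.8416)² × (0.25 + 0.25) / 0.10² = 392.4, so 393 per arm, which agrees with 400. Sidedness is not stated; one-sided 5% gives 310.

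**2. What efficacy alone needs.** 2 × (1.96 + 0.8416)² × (10/5)² = 62.8, so 63 per arm. The rank test with normal data needs 62.8 × π/3 = 65.8, so 66. Non-inferiority drives the 400.

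**3. Sensitivity at 400 per arm.** The standard error of the mean difference is 10 × √(2/400) = 0.707.

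- Smallest significant observed difference, and CI half-width: 1.96 × 0.707 = 1.39 points.
- Power at a true difference of 2 points: Φ(2/0.707 − 1.96) = 0.807. A simulated Mann-Whitney test (4,000 runs) gave 78%.
- Power at 5 points: Φ(5/0.707 − 1.96), above 99.9%.

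**4. What an interval adds.** The 95% CI is the observed difference ± 1.39. It lies wholly below 5 for observed differences under 5 − 1.39 = 3.61. Any observed gain between 1.39 and 3.61 points is therefore significant while the CI excludes the relevant difference. The whole CI lies above 5 only when the observed gain exceeds 6.39. The p-value alone does not show readers which of these cases they are in.

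**5. Ignoring centre.** Stratified randomisation removes centre variation from the true error of the comparison, but the pooled test still counts it. Its standard error is too large by 1/√(1 − ICC), and the actual two-sided alpha is 2 × [1 − Φ(1.96/√(1 − ICC))].

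| Assumed ICC | Standard error ratio | Actual alpha | Simulated alpha, Mann-Whitney |
|---|---|---|---|
| 0.02 | 1.010 | 4.8% | 4.9% |
| 0.05 | 1.026 | 4.4% | 5.1% |
| 0.10 | 1.054 | 3.9% | 4.0% |

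The error rate is not inflated by the formula, and the simulation agrees within its own noise.

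**6. Gain from adjustment.** The half-width becomes 1.386 × √(1 − R²).

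| Assumed R² | Half-width (points) |
|---|---|
| 0 | 1.39 |
| 0.10 | 1.31 |
| 0.20 | 1.24 |
| 0.25 | 1.20 |
| 0.50 | 0.98 |

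**The case against.** The strongest reply is that the planned test is sound. Its error rate is at or slightly below nominal, its power at 5 points is above 99.9%, and the rank test costs only 66 against 63 per arm when 400 are enrolled. No primary conclusion is shown to change. All of this stands.

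It is also fair to say that the article is condensed and that an unseen analysis plan may add an estimate, covariates or strata. That limits the weight of the point but does not remove it: the article names a specific primary test, and that test remains primary unless it is changed. The promise to report by CONSORT governs the report and does not fix which effect measure is primary.

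Four stronger readings are tempting and are not supported.

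- *The rank test causes small gains to be declared superior.* The 1.4-point and 81% figures follow from 400 per arm and a null of zero. A t-test or an adjusted model tested against zero behaves the same way, and adjustment raises power at 2 points to about 85% at R² 0.10. The remedy is the reported interval, not a different test against zero. Nor does the protocol say that significance will be read as proof of 5 points.
- *Baseline weight is ignored.* Primary endpoint makes presurgical weight the reference for %TWL. What goes unused is baseline BMI as a covariate.
- *The intention-to-treat analysis is complete-case and dropouts are discarded.* A single-visit rank test needs a value for each patient, but that value can be imputed. Analysis of endpoints keeps all randomised patients, excludes missed measurements only from the per-protocol set, and adds: "Additional sensitivity analysis will be used if, despite all efforts taken to ensure complete data collection, the number of missing data is non-negligible". The imputation method may stand in the analysis plan.
- *A distribution-free test is wrong here.* That normality is not needed at this size shows only that a mean comparison is also acceptable.

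**Conclusion.** The point holds as a recommended improvement, not as an error that threatens the trial's validity. The protocol fixes an efficacy analysis that leaves out the randomisation strata and baseline BMI, and it plans no estimate in the units of its own 5-point threshold. The main loss is interpretive: significance starts at about 1.4 points, and between 1.39 and 3.61 observed points the result would be significant although the CI excludes 5. These figures assume the protocol's SD of 10 and complete data on 400 per arm.

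The loss of precision is modest and rests on assumed values: a standard error 1-5% too large at ICC 0.02-0.10, and a half-width of 1.39 falling to 1.31-1.24 at R² 0.10-0.20. The sample size of 400 per arm is unaffected.

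**What to change.** - **Primary efficacy analysis:** replace the plain Mann-Whitney test with a centre-stratified model adjusted for baseline BMI. This can be an ANCOVA of 5-year %TWL, or a mixed model over the recorded postoperative visits with arm-by-visit and BMI-by-visit terms and centre. The mixed model also uses the earlier weights of patients without a 5-year weight, under a missing-at-random assumption, and yields the 1- and 3-year contrasts.
- **Reporting:** give the 5-year mean difference in %TWL with its 95% CI. Test superiority against 0, and state separately whether the CI lies below, includes or lies above 5 points.
- **Sensitivity analysis:** a centre-stratified (van Elteren) rank test.
- **If a rank test stays primary:** use van Elteren with a Hodges-Lehmann difference and its CI.
- **Secondary endpoint:** %EBMIL follows the primary analysis, so the same change carries over.

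The cost is wording in the protocol and analysis plan. No patients, visits or measurements are added. The small downside is that a model replaces a distribution-free test, which the rank-based sensitivity analysis covers.

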### Primary objective

The primary objective of this study is to show that long BPL leads to a greater percent total weight loss (%TWL, superiority), while not leading to a larger nutritional deficiency rate (non-inferiority) at 1-, 3-, and 5-year follow-up.

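### The stated safety analysis gives one confidence interval per arm and never sets a between-arm difference against the 10% non-inferiority margin

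*Protocol article*

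**What the plan says.** Under Primary objective, the long limb should give greater weight loss "while not leading to a larger nutritional deficiency rate (non-inferiority) at 1-, 3-, and 5-year follow-up". Under Primary endpoint: "The primary endpoints are %TWL and the number of nutritional deficiencies 1, 3, and 5 years postoperatively".

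The Sample size section assumes "an expected cumulative nutritional deficiency rate of 50% at 5 years follow-up" and continues "with a non-inferiority margin defined at 10%, 400 patients per group will be needed to reach a power of 80" per cent, with alpha at 5%. It then refers the reader to the analysis section for details of the calculation.

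The section Analysis of primary endpoint announces two separate analyses, one for efficacy and one for safety. Efficacy gets a between-arm Mann-Whitney U test. Safety gets this: "The proportion of safety events during the first 5 years in each study arm is reported, including the two-sided 95% confidence interval".

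The general section Analysis of endpoints defines the intention-to-treat (ITT) and per-protocol (PP) populations. Neither it nor the section on secondary endpoints contains a between-arm safety contrast, and neither mentions the margin. The margin appears only under Sample size.

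**The concern.** A non-inferiority claim is a statement about a difference: the excess in the experimental arm must be shown to lie below the margin. Two separate intervals, one per arm, do not make that statement. The article is not silent here. It states an analysis, and that analysis does not fit the objective that it is meant to serve.

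At stake is the safety half of the primary objective. If the section is followed as written, the trial reports two proportions with their intervals and has no rule for saying whether the long limb met the margin. Any rule would then be chosen with the data in view.

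**Working it through.** **Inputs** (Sample size and Randomization sections): expected 5-year deficiency rate 50%, taken as equal in both arms; margin 10%, read as 10 absolute points; power 80%; alpha 5%, sidedness not stated; 400 per arm, 1:1. For efficacy: difference 5 points of %TWL, SD 10.

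**1. Reproduce the planned size.** For non-inferiority of two proportions, n per arm = (z₁₋α + z₁₋β)² × [p₁(1−p₁) + p₂(1−p₂)] / margin².

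- One-sided 2.5%: (1.960 + 0.842)² × 0.50 / 0.10² = 392.4, so 393 per arm. This agrees with 400 to within 2%.
- One-sided 5%: 310 per arm, which does not match.
- Margin read as 10% relative (5 points at a 50% rate): about 1,570 per arm, which does not match.

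The planned size therefore fits a 10-point absolute margin judged by a two-sided 95% interval for the difference.

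**2. What efficacy alone would need.** 2 × (1.960 + 0.842)² × 10² / 5² = 62.8, so 63 per arm. The non-inferiority comparison drives the 400.

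**3. Width of the intervals at 50% and 400 per arm.**

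- Each arm: 1.96 × √(0.25/400) = 0.049, or ±4.9 points.
- Difference: 1.96 × √(0.50/400) = 0.0693, or ±6.9 points.

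**4. What a margin test requires.** The upper limit is below 10 points when the observed excess is at most 10 − 6.93 = 3.07 points. Power at no true difference is Φ(0.10/0.03536 − 1.96) = Φ(0.868) = 80.7%.

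**5. Why two per-arm intervals cannot replace it (hypothetical rules, neither in the protocol).**

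- *Overlap read as non-inferiority.* At 50% in each arm the intervals overlap up to an excess of about 2 × 4.9 = 9.8 points. At true rates of 60% and 50% the half-widths are 4.80 and 4.90 points, and the standard error of the difference is √(0.24/400 + 0.25/400) = 3.5 points. The chance of overlap is Φ((9.70 − 10)/3.5) ≈ 46.6% by the normal approximation. Exact enumeration over the two binomial distributions gives 45.7%. The margin test passes 2.5% of the same trials.
- *Upper limit of long minus lower limit of short below 10 points.* Power at no true difference is Φ((0.10 − 0.098)/0.03536) ≈ 52%, instead of about 81%.

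One rule is far too lenient and the other far too strict. The per-arm intervals do not say which to use.

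**The case against.** The strongest reply is that the design is clear. The hypothesis type, margin, alpha, power and both analysis populations are fixed, and the planned size matches a two-sided 95% interval for a difference. The document is a condensed article, and placing that interval against a stated margin is a step that an analysis plan commonly spells out. The wording on the confidence interval could be loose shorthand for the interval of the difference.

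Much of this stands. The intent is evident and the sample size is sound. A reader might infer that the sponsor will never test non-inferiority, but an analysis plan that is not shown may contain the test. What does not stand is that the text is merely brief. It attaches the interval to the proportion in each arm, while efficacy in the same paragraph gets a named between-arm test. Even on the loose reading, no margin and no criterion are given, and the pointer from Sample size leads to no such method.

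Two further inferences are tempting and unsupported:

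- *That patients who leave before a first deficiency count as event-free, which would pull the arms together.* The article says who belongs to the ITT population, not how missing outcomes are scored. It calls the rate cumulative, and it foresees sensitivity analysis if missing data matter.
- *That the trial will judge non-inferiority by overlapping intervals.* No section proposes this. The 46% shows only what such a reading would cost.

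**Conclusion.** The point holds as a mismatch between the stated analysis and the declared objective. Non-inferiority on nutritional deficiency is half of the primary objective and drives 400 per arm (393 recomputed, against 63 for efficacy). Yet the analysis sections contain no between-arm safety contrast and no use of the margin. Followed as written, they give no non-inferiority decision.

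The figures rest on a 50% rate in both arms (60% against 50% for the illustration at the margin), 400 evaluable patients per arm, a margin of 10 absolute points and one-sided 2.5%. The article does not state the last two outright, but they are the readings that reproduce its sample size. The defect lies in the stated analysis, not in the number of patients.

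**What to change.** Replace the safety sentence under Analysis of primary endpoint with:

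*The difference (long minus short BPL) in the 5-year cumulative nutritional deficiency rate is estimated with a two-sided 95% confidence interval. Non-inferiority is concluded if the upper limit is below 10 percentage points. The analysis is done in the ITT and PP populations already planned. The primary objective is met only if both this and the %TWL superiority test succeed.*

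A simple difference in proportions is enough to close the gap. Time-to-event estimation and centre stratification are optional choices. The wording does not make success in the PP population a condition: that population drops anyone with missed measurements, so such a condition would cost power.

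The replacement uses the 5-year rate because the sample size does. The endpoint section instead speaks of a number of deficiencies and also names years 1 and 3, so the sponsor should confirm that the 5-year rate carries the decision.

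The cost is one change of wording in the protocol, mirrored in the analysis plan, with no new data and no change in sample size.
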